### Sample size

Based on existing literature [37], with a success rate in brief (p1) and intensive (p1) intervention arm of 16.8% and (p2) 30.3% respectively, we expected a difference of approximately 13.5% in cessation rates between the two groups. Sample size was calculated using the Sealed Envelope Ltd. 2012 software application. Power calculator for binary outcome superiority trial based on the formula *n* = *f*(α/2, *β*) × [*p*1 × (100 − *p*1) + *p*2 × (100 − *p*2)]/(*p*2 − *p*1)2 and *f*(*α*, *β*) = [*Φ*-1(*α*) + *Φ*-1(*β*)]2, where *Φ*-1 is the cumulative distribution function of a standardized normal deviate. The alpha level (*α*) at 0.05 and power (*β*) 80% was set to detect a clinically significant difference between the two arms. Sample size was inflated using 20% dropout rate making a total sample size of 366. Participants will be randomly assigned into two arms at a ratio of 1:1 with 183 in each arm. The planned sample size will be recruited in approximately 3 months and followed up for 6 months.

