**Methods/design:**

A two-arm randomized controlled trial (RCT) in a tertiary healthcare hospital will be performed. A total of 360 tobacco users attending NCD clinics in four departments, cardiology, neurology, pulmonary medicine, and ENT (otolaryngology), will be recruited over a period of 3 months. After ascertaining the eligibility criteria, they will be followed up to 6 months (1, 3, 6) for their tobacco use status, readiness to quit, nicotine dependence, stage of behavior change, and self-reported and biochemical validation (urine cotinine) for tobacco abstinence. Assignment of intervention including allocation concealment, sequence generation, and blinding will be done as per SPIRIT guidelines for RCT protocols.

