### Inclusion, exclusion, and dropout/withdrawal criteria

Participants will be eligible provided they (1) are above 18 years of age, (2) have a history of using tobacco for the last 1 month and at least 10 pack-year or equivalent tobacco, (3) can read and understand English, Hindi, or Punjabi, (4) have a mobile phone with text messages/WhatsApp messages accessibility, and (5) are willing to quit and provide written consent for intervention and follow-up of 6 months in the study.

Participants will be excluded if they (1) are unable to understand any of the languages as mentioned above, (2) are severely ill to participate in the study and require urgent attention for any of the medical problems, (3) are already taking treatment for tobacco cessation, and (4) are mentally ill to accord informed consent for the study.

Participants will be discontinued for the study if they (1) voluntarily withdraw the consent, (2) are not complying with the study schedule, and (3) are not in a condition to continue with the study due to migration or other reasons. The reason for withdrawal will be collected, and no more follow-up will be initiated. Participants who drop out of the study will be considered tobacco users.

Intention-to-treat will be used for data analysis, wherein all participants who are randomized to a treatment arm and receive their assigned intervention are included in the final analysis whether they complete the study or respond to follow-up surveys at study end points. This method will be used to avoid any bias that can potentially arise because of crossover and dropouts, affecting the initial random assignment to treatment groups.

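### The total of 366 comes from multiplying 152 per arm by 1.2, which does not preserve 80% power at 20% dropout; what 183 per arm delivers (about 76%, 79% or 87%) depends on two points the protocol leaves open

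*Protocol article*

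**What the plan says.** All of this is in the protocol article.

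- **Sample size:** the literature success rates are given as "intervention arm of 16.8% and (p2) 30.3% respectively", with a two-sided alpha of 0.05 (the formula uses α/2). On power: "80% was set to detect a clinically significant difference between the two arms". On attrition: "Sample size was inflated using 20% dropout rate making a total sample size of 366", split 1:1 as 183 per arm.
- **Inclusion, exclusion, and dropout/withdrawal criteria:** "Participants who drop out of the study will be considered tobacco users". The same section keeps participants in the intention-to-treat analysis whether or not they complete follow-up.
- **Data analysis:** the primary outcome is analysed by intention to treat, and missing data are to be handled by multiple imputation.
- **Abstract, Methods/design:** "A total of 360 tobacco users attending NCD clinics in four departments".

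The article does not say whether the two literature rates are among participants followed up or among all randomised with dropouts counted as failures.

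**The concern.** An allowance for dropout should leave the required number of evaluable participants once the losses have occurred. Multiplying by 1 + d does not do that; dividing by 1 − d does. That slip is small.

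The larger issue is that the allowance and the dropout rule describe different analyses. Inflating the sample size makes sense if dropouts are removed. If they stay in as tobacco users, the analysed number does not fall. Both quit rates shrink instead, and so does the difference to be detected. A larger sample chosen to replace lost participants is not sized to offset a smaller difference.

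At stake is how the result is read. A null finding would be judged against a stated 80% that does not follow from the stated inputs. The abstract's different total adds doubt about which design is in force.

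**Working it through.** **Inputs:** p1 = 0.168, p2 = 0.303, two-sided alpha 0.05, power 80%, dropout 20%, 183 per arm (Sample size); dropouts counted as users (withdrawal criteria); total 360 (Abstract). Equal dropout in the two arms is my assumption.

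**1. Reproduce the plan's figure.** The plan's formula is n = f × [p1(1 − p1) + p2(1 − p2)]/(p2 − p1)², with f = (1.960 + 0.842)² = 7.849.

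- Variance term: 0.168 × 0.832 + 0.303 × 0.697 = 0.35097.
- n = 7.849 × 0.35097/0.135² = 151.15, so 152 per arm.
- 152 × 1.2 = 182.4, rounded up to 183 per arm, 366 in total. This matches exactly.

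The other versions tried do not give 366. The pooled two-sided formula gives 154 per arm (370 after × 1.2), with continuity correction 169 (406); the pooled one-sided formula gives 122 (294).

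**2. Inflation that preserves 152 evaluable.** 152/0.8 = 190 per arm, 380 in total.

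**3. Power if dropouts are excluded.** 183 × 0.8 = 146.4 completers per arm. Power = Φ(0.135/√(0.35097/146.4) − 1.960) = Φ(2.757 − 1.960) = 78.7%. A pooled test gives 78.0%.

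**4. Power if dropouts count as users and the cited rates are among those followed.**

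- Diluted rates: 0.8 × 16.8% = 13.44% and 0.8 × 30.3% = 24.24%. The difference is 10.8 points instead of 13.5.
- Variance term: 0.1344 × 0.8656 + 0.2424 × 0.7576 = 0.29998.
- Power at 183 per arm = Φ(0.108/√(0.29998/183) − 1.960) = Φ(2.667 − 1.960) = 76.0%. A pooled test gives 75.5%.

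The same calculation at other dropout rates, 183 per arm:

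| Dropout in both arms | Rates | Power |
|---|---|---|
| 10% | 15.1% vs 27.3% | 82.0% |
| 15% | 14.3% vs 25.8% | 79.2% |
| 20% | 13.4% vs 24.2% | 76.0% |
| 25% | 12.6% vs 22.7% | 72.7% |

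At 20% dropout, 190 per arm gives only 77.6% under this rule, so correcting the inflation alone would not restore 80%. About 202 per arm would be needed (7.849 × 0.29998/0.108² = 201.9).

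**5. Power if the cited rates already count dropouts as failures.** No dilution and no loss apply: Φ(0.135/√(0.35097/183) − 1.960) = Φ(3.083 − 1.960) = 86.9%.

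**6. 360 against 366.** At 180 per arm, the step 4 power is 75.4%, a change of 0.6 points.

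**The case against.** A reader might infer that the trial is simply underpowered at 76%. The document does not support that as an unconditional statement, for four reasons.

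- **Basis of the rates.** The 76% needs 16.8% and 30.3% to be rates among those followed. Inflating for dropout suggests this, but such inflation is often applied by routine and the article does not state it. If the source counted dropouts as failures, 183 per arm exceeds the target at about 87%.
- **Competing rule.** Data analysis prescribes multiple imputation for missing data. If that governs some or all missing 6-month outcomes, the full dilution does not apply. The sentence counting dropouts as users stands among the withdrawal criteria and may not reach every missed urine sample.
- **Dependence on dropout.** At 10% dropout the same rule gives 82%.
- **Size and consequence.** The × 1.2 slip alone costs about 1.3 points against 80%, and 360 versus 366 less than one. Recruitment is under way, and the planned 95% confidence interval will show the precision of a null result whatever power was stated.

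All four stand, and they limit the severity. They do not rescue the statement as written. The multiplication by 1.2 misses the plan's own requirement at the plan's own dropout rate, and 80% is not the power of 183 per arm under any of the readings worked through. Nor is this detail left to an analysis plan: the inflation, the dropout rule and both totals are printed in the article.

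**Conclusion.** The point holds, at moderate severity. It is certain that 366 is 152 × 1.2, that 380 would be needed to keep 152 evaluable per arm after 20% loss, and that the abstract and the Sample size section give different totals.

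The power at 183 per arm with 20% dropout is conditional:

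- about 79% on completers;
- about 76% with dropouts counted as users and the cited rates taken among those followed;
- about 87% if the cited rates already include dropouts as failures.

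The first two fall short of 80% and the third exceeds it. The figures rest on the plan's unpooled normal formula and equal dropout in both arms; a pooled test lowers each by less than one point. They do not show that the trial is invalid or that more participants must be recruited.

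**What to change.** Leave recruitment as planned and correct the text in this order:

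1. In Sample size, say whether 16.8% and 30.3% are rates among participants followed up or among all randomised with dropouts counted as failures.
2. Reconcile the withdrawal criteria (dropouts counted as users) with Data analysis (multiple imputation), so that one rule governs missing 6-month status in the primary outcome.
3. Replace the 80% claim with the power that 183 per arm gives under those choices. If dropouts count as users and the rates are among those followed, for example: *With 20% dropout in each arm, 183 per arm gives about 76% power (13.4% versus 24.2%).* If the analysis is on completers, the figure is about 79%; if the rates already include dropouts as failures, about 87% with no inflation needed. If imputation is chosen, calculate the power for that analysis.
4. Give one total, 360 or 366, in both the Abstract and Sample size.

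The cost is wording only. Under two of the three readings the stated power becomes slightly less favourable. No figure should be printed before steps 1 and 2 are settled, because the wrong choice would put a new error in place of the old one.

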### Assignment of intervention

The PhD scholar (primary author of study) from the Department of Community Medicine and School of Public Health will administer the intervention. She is a dental graduate and has Masters in Public Health (MPH) degree with necessary skills of community intervention and counseling during her training. Also, she witnessed and attended training sessions delivered by counselors and psychiatrist in Drug De-Addiction Treatment Centre of the institute for a period of 3 months, prior to the delivery of intervention.

#### Sequence generation

The participants meeting the inclusion criteria will be randomly assigned by the researcher to either control or intervention arm with a 1:1 allocation as per the randomization sequence generated in advance by a computer program. To ensure a balanced representation of the participants in two groups from various departments, stratified block randomization will be used.

#### Allocation concealment

To ensure and prevent participants and researcher from knowing the study group to which the next participant will be assigned, concealment of allocation will be maintained using sequentially numbered, opaque sealed envelopes. One of the study members other than the researcher will create the allocation sequence in the opaque envelopes for assigning the intervention group, which the researcher will then open for participants’ enrolment.

#### Implementation

Prior to opening envelopes, the eligibility of participants shall be assessed by the researcher. Eligible participants will then be informed about the trial and asked for their participation. After that, the interested participants will then be enrolled in the intervention arms and provided with the assigned intervention by the study researcher.

#### Blinding

The study will be open-label, where participants assigned to the intervention arm will not be blinded, in addition the person delivering the intervention and assessing the outcome (researcher) will be aware of the intervention group to which participants have been assigned (Fig. 1).

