	(Motivational videos) Videos based on real life stories of patients with tobacco use history will educate and sensitize patients and care givers on harmful effects of tobacco and motivate patients to quit	3–5 min/once during first contact/researcher	Technology including mobile phones, the internet, and social media platforms, can increase access to care by extending the work of counselors and overcoming the geographical barriers. These supports can increase the likelihood of adults quitting compared with no intervention and can be a cost-effective adjunct to other treatments [39]
	(Patient information leaflet (PIL)) Patient information leaflet will be based on specific characteristics or concerns of tobacco users and include written material aiming to educate patients about the disease, ill effects of using tobacco on health, benefits of quitting and how to resist cravings and avoid relapse	Once at first contact/researcher	Providing self-help materials (primarily print-based) tailored to the individual patient (that is, beyond a brochure that simply describes the health effects of tobacco use and benefits of cessation) is effective in improving tobacco abstinence [40]
**Intensive**	(Telephone counseling) Counseling through regular telephone follow-up will provide support and encouragement to individuals who uses tobacco and want to quit or individuals who have recently quit	05–15 min/five times at < 1, 4, 6, 9, and 12 weeks in 3 months after enrolment/researcher	Telephone-based access to counseling and smoking cessation resources increases cessation rates. The majority of helplines provide access to individual counseling; the greatest amount of counselor contact, the greater the likelihood of successful cessation [41]
	(Text messages using SMS) Messages will include short text based on the current stage of behavior as per trans-theoretical model for their motivation and support regarding tobacco cessation and maintaining quit status	Bi-weekly for 3 months/researcher	Technology, including mobile phones, the internet, and social media platforms, has the power to increase access to care by extending the work of counselors and overcoming geographical barriers. These supports can increase the likelihood of adults quitting compared with no intervention and can be a cost-effective adjunct to other treatments [39]

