### Data collection

After fulfilling the inclusion criteria and seeking written consent, the researcher will collect data from tobacco users enrolled in the study. Baseline and end of follow-up (6 months) of intervention assessment will include assessment of tobacco use (daily tobacco consumption, age of initiation, quit attempt, treatment sought for cessation (if any)); knowledge, attitude, and practices about tobacco use.

The assessment of motivation to quit tobacco will be undertaken using Readiness to Change questionnaire [42] (RCQ), nicotine dependence using FTND scale [43], and stages of behavior change using a trans-theoretical model of behavior change at each follow-up (0, 1, 3, 6) months. The self-reporting assessment for 7-day point prevalence and continuous tobacco abstinence will also be done at each (0, 1, 3, 6) follow-up month. In addition, a urine sample will be collected at the last follow-up (6 months of intervention) to confirm the cotinine presence biochemically (Table 2).

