### Data analysis

Data analysis will be undertaken by the investigators using the SPSS statistical analysis package.

Analysis of primary outcome of 7-day point prevalence tobacco abstinence at 6 months will be based on an intention-to-treat approach. It shall be done by estimating the mean difference in percentage of quit rates between the intensive and brief intervention groups at 6 months.

Regression analysis and /or ANOVA will be used for primary and secondary outcomes. For not normally distributed data, robust standard errors, truncation, or transformation will be used. For missing data, multiple imputations will be used. The net changes in primary and secondary outcome measures will be considered by exploratory analysis. Marginal means and treatment effect with its associated 95% CI and probability values will be presented and reported. The conventional significance level of 0.05 will be used in all analyses to reject the null hypothesis of no difference between two groups.

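### The researcher who counsels both arms, and phones and texts only the intensive arm, also collects the self-reported outcomes knowing the arm; the 1- and 3-month reports are unverified and the abstract implies blinding

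*Protocol article*

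**What the plan says.** The protocol article describes an unblinded trial in which one researcher holds several roles.

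- **Delivery.** Under Assignment of intervention, a PhD scholar "from the Department of Community Medicine and School of Public Health will administer the intervention".
- **Knowledge of arm.** Under Blinding: "The study will be open-label, where participants assigned to the intervention arm will not be blinded". The same sentence adds that "the person delivering the intervention and assessing the outcome (researcher) will be aware of the intervention group to which participants have been assigned".
- **Data collection.** Under Data collection, "the researcher will collect data from tobacco users enrolled in the study". Self-reported 7-day and continuous abstinence, readiness to change and nicotine dependence are assessed at 0, 1, 3 and 6 months. Urine is taken at 6 months only.
- **Contact by arm.** In Table 1 (Intervention/treatment arm) both arms receive one face-to-face counselling session, a video and a leaflet from the researcher. The intensive arm alone also receives text messages for 3 months and telephone counselling "five times at < 1, 4, 6, 9, and 12 weeks in 3 months after enrolment", again from the researcher.
- **Abstract.** Its Methods/design paragraph says that "allocation concealment, sequence generation, and blinding will be done as per SPIRIT guidelines for RCT protocols".

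The limitations listed in the Discussion do not mention unblinded outcome assessment.

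**The concern.** Open-label delivery cannot be avoided in a counselling trial. Having the counsellor collect the self-reports is a separate choice, and it can be changed. A participant who has been coached repeatedly by the person now asking about tobacco use may be more inclined to report success. The coaching after first contact is given to one arm only, so any such inclination is likely to be stronger there.

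The exposed outcomes are the secondary ones that rest on self-report: continuous and 7-day abstinence, reduction in use, readiness to change, nicotine dependence, and quit attempts and relapses. The exposure is greatest at 1 and 3 months, when nothing checks the report. The protocol itself faults earlier research for relying on self-report (Background) and argues that biochemical verification adds rigour (Discussion). Yet it presents the effects at 1, 3 and 6 months as a strength without this caveat. A reader of the abstract alone would also believe that some form of blinding exists.

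**Working it through.** **1. Timing.** Months are converted to weeks as months × 365.25 / 12 / 7.

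| Assessment | Weeks | Nearest intensive-arm call | Gap | Urine check |
|---|---|---|---|---|
| 1 month | 4.3 | week 4 | about 0.3 weeks | no |
| 3 months | 13.0 | week 12 | about 1 week | no |
| 6 months | 26.1 | week 12 | about 14 weeks | yes |

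**2. Contact.** Both arms have one session of 10–20 minutes. The intensive arm adds five calls of 5–15 minutes, which is 25–75 minutes, plus text messages.

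**3. Over-reporting and the self-reported difference.** The documents give no over-reporting rate, so every rate here is an assumption. Let p be the true abstinence rate and r the share of continuing users who report abstinence. The shift in the difference (intensive minus brief) is r_I(1 − p_I) − r_B(1 − p_B). The Sample size section's rates, p_I = 0.303 and p_B = 0.168, serve only as illustrative true rates.

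- r_I = 5%, r_B = 0: 0.05 × 0.697 = 0.035, or 3.5 points.
- r_I = 10%, r_B = 0: 0.10 × 0.697 = 0.070, or 7.0 points.
- r_I = 10%, r_B = 5%: 0.0697 − 0.05 × 0.832 = 0.0697 − 0.0416 = 0.028, or 2.8 points.
- r_I = r_B = 5%: 0.0349 − 0.0416 = −0.007, or −0.7 points.

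Equal over-reporting does not favour the intensive arm; only a differential does. Setting r_B = 0 is the extreme case, because the brief arm also reports to the person who counselled it.

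**4. False findings on a self-reported outcome.** The planned 183 per arm reproduces from the article's own formula: (1.960 + 0.842)² × [0.168 × 0.832 + 0.303 × 0.697] / 0.135² = 151.15, so 152; 152 × 1.2 = 182.4, so 183.

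Take no true effect, reported rate p in the brief arm and q = p + b in the intensive arm, with m = (p + q)/2 and n per arm. The chance of a significant result favouring intensive is Φ{[b − 1.96√(2m(1 − m)/n)] / √[(p(1 − p) + q(1 − q))/n]}.

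For p = 0.168, b = 0.05, n = 183: [0.05 − 1.96 × 0.04126] / 0.04117 = −0.75, which gives 22.7%.

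| Net excess b (assumed) | p = 16.8%, n = 183 | p = 30.3%, n = 183 | p = 16.8%, n = 146 | p = 30.3%, n = 146 |
|---|---|---|---|---|
| 2 points | 7.2% | 6.1% | 6.5% | 5.6% |
| 3 points | 11.1% | 8.9% | 9.7% | 7.9% |
| 5 points | 22.7% | 17.3% | 19.0% | 14.7% |
| 8 points | 47.0% | 36.3% | 39.1% | 30.1% |

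The nominal rate for that tail is 2.5%. The n = 146 columns allow for the planned 20% dropout (183 × 0.8 = 146.4).

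**5. Abstract against Methods.** The abstract lists blinding among the things that will be done. The Blinding section calls the trial open-label and describes no masked role. Even if the abstract means only that blinding is reported in line with a guideline, its wording claims a property that the Methods do not describe.

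**The case against.** The strongest reply is that the design is openly disclosed, and that the outcome carrying the hypothesis is verified by cotinine, precisely because self-report is weaker. A different study member prepares the sealed envelopes, so concealment is not at issue. All of this stands, and it confines the point to secondary outcomes and reporting.

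Three stronger inferences are tempting and are not supported.

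- **That the brief arm has no relationship with the assessor.** Table 1 gives both arms face-to-face counselling from the same researcher. The arms differ in the amount of later contact.
- **That assessments take place during the counselling calls.** No section says that a call and an assessment are one contact, and the schedule table is not reproduced in the text available. The dates are near at 1 and 3 months, and no call is near 6 months.
- **That the assay is read, or the data analysed, with knowledge of arm.** The Data analysis section says only that "Data analysis will be undertaken by the investigators using the SPSS statistical analysis package". Masking of the laboratory or analyst is a detail that an article commonly leaves to the full protocol, so silence on it is no finding.

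It can also be said that self-completion may do harm. Participants still know their arm. The brief arm, with less contact, may respond less. The article counts dropouts as tobacco users; if non-responders were treated likewise, this would favour the intensive arm too. For example, if 10% more of the brief arm failed to respond and 16.8% of those were abstinent, its rate would fall by 0.10 × 0.168 = 1.7 points. This stands, and the fix has to deal with it.

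**Conclusion.** The point holds as a risk of bias in the self-reported secondary outcomes, chiefly the unverified 1- and 3-month ones, together with a wording conflict between the abstract and the Blinding section. The documents do not show that bias occurs. Its likely direction favours the intensive arm, and its size depends wholly on assumed over-reporting: a net excess of 2 to 5 points raises the false-finding rate on such an outcome from 2.5% to between 5.6% and 22.7% across the base rates and sample sizes tried.

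A reader might set these shifts against the 13.5-point planned difference and conclude that the main result is in doubt. That does not follow. The trial's hypothesis concerns cotinine-verified abstinence at 6 months, whereas the shifts apply to unverified reports. The 6-month self-reports are also collected unblinded, but the urine sample gives a check on recent use at that visit.

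This is a worthwhile, low-cost improvement and does not threaten the primary analysis.

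**What to change.** 1. Have participants complete the 1-, 3- and 6-month self-report items themselves, by message or paper form, before any counselling contact at that time point. Eligibility already requires reading ability and a phone with messaging.
2. Use the same scripted fallback for non-completers in both arms, and report response and mode of completion by arm, because non-response may be higher in the brief arm.
3. Label urine samples with study number only, so that cotinine is read without knowledge of arm. This is a precaution; the article does not say otherwise.
4. Correct the abstract to describe the trial as open-label. Mention masked roles only if they are adopted.
5. Add to the limitations in the Discussion that self-reported outcomes were assessed unblinded and that those at 1 and 3 months were not biochemically verified.

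The cost is a short form, coded labels and two text edits, with no extra staff. The fallback contact brings back some researcher involvement, and participants' own knowledge of their arm remains. The article reports recruitment as ongoing, so items 1 to 3 would apply only to assessments still to come, and the date of the change should be recorded. Items 4 and 5 can be made at any time.
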